## 2. Problem Statement and Justification

Patients under mechanical ventilation (MV) in the intensive care unit (ICU) exhibit high hospital mortality rates, ranging from 23% to 51%. This mortality is linked to the success of weaning and the incidence of nosocomial infections. Prolonged MV can increase complications in critically ill patients, extending immobility and raising the risk of ventilator-associated pneumonia, further restricting patients. It is argued that early mobility improves MV-related outcomes, such as ventilator duration and ventilator-free days, breaking the vicious cycle of prolonged MV and immobilization. Additionally, early rehabilitation is associated with reduced morbidity and mortality, as well as complications of the disease, ICU length of stay, hospital stay, and rehospitalization rate. Therefore, weaning from MV through early rehabilitation is crucial to improving the prognosis of ICU patients.

Despite the growing evidence on the utility of early rehabilitation for critically ill patients, programs and interest in outcomes vary among studies. Given this diversity, healthcare professionals must assess whether different programs have a similar therapeutic effect and ensure that the prescribed rehabilitation provides benefits consistent with previous literature. Besides the heterogeneity among programs, different countries and institutions face barriers to implementation, such as a shortage of trained rehabilitation personnel and a cultural gap in the ICU. In cases of personnel

shortages and settings with conservative ICU ethics, early rehabilitation is adapted to a sustainable level, including modified programs or less frequent visits.

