## 6.6. Outcomes

### *Effectiveness*

Main outcome: time (days) from intubation to extubating.

- Secondary outcomes:

- Days free of mechanical ventilation until day 28
- Days of delirium until day 28
- Time in ICU with delirium until day 28
- Days of hospitalization with delirium until day 28
- Days of sedation until day 28
- Sedation-free days until day 28
- Extubating failure
- Need for non-invasive mechanical ventilation
- Exploratory outcomes:
- Barthel index at discharge
- Days of hospital stay
- Length of stay in ICU
- Mortality from any cause up to 90 days
- Time from intubation to start of therapy
- Muscular strength measured with the Medical Research Council (MRC) scale
- Dysphagia 72 hours after extubation
- Dysphonia 72 hours after extubation
- Time until initiation of oral administration post-extubation
- Development of healthcare-associated pneumonia,
- Maximum mobility measured by JH-HLM
- Grip strength
- Cognitive function measured using the Montreal Cognitive Assessment (MOCA)
- Evaluation of functionality in daily activities until day 28
- Quick sensitivity and dexterity test

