| Days from the start of ventilatory support to the start of weaning | Days from the start of ventilatory support (intubation) to the start of weaning                                                                                                                   | Discrete Quantitative   | Days                                                                                                                                                                                                     |
| Days of mechanical ventilation                                     | Days of invasive mechanical ventilation                                                                                                                                                           | Discrete Quantitative   | Days                                                                                                                                                                                                     |
| Days free of mechanical ventilation                                | 28 days minus ventilation days                                                                                                                                                                    | Discrete Quantitative   | Days

It will be defined as 0 if the patient dies or has been ventilated for more than 28 days.                                                                                                    |
| Delirium                                                           | For a patient to be considered to have delirium according to the CAM-ICU, both the first criterion (acute alteration in mental status) and at least one of the other three criteria (inability to | Qualitative Nominal     | 
 
1. Acute alteration of mental status (+/-).
 
2. Inability to maintain sustained attention (+/-).
 
3. Disorganization of thought (+/-).
 
 |

|                                          |                                                                                                                                |                       |                                                        |
|------------------------------------------|--------------------------------------------------------------------------------------------------------------------------------|-----------------------|--------------------------------------------------------|

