|                                          | maintain sustained attention, disorganization of thought, or fluctuating changes in level of consciousness).                   |                       | 4. Fluctuating changes in level of consciousness (+/-) |
| Days of delirium                         | Days with the presence of delirium                                                                                             | Discrete Quantitative | Days                                                   |
| Sedation days                            | Days with sedation                                                                                                             | Discrete Quantitative | Days                                                   |
| Sedation-free days                       | 28 days fewer days of sedation                                                                                                 | Discrete Quantitative | Days
It will be defined as 0 if the patient dies.   |
| Barthel index at hospital discharge      | The Barthel Index is a scale used to measure a person's degree of functional independence in activities of daily living (ADL). | Discrete Quantitative | It will be 0 if the patient dies.                      |
| Days of hospital stay                    | Days of hospital stay                                                                                                          | Discrete Quantitative | Days                                                   |
| Days of ICU stay                         | Days of ICU stay                                                                                                               | Discrete Quantitative | Days                                                   |
| Mortality                                | Death                                                                                                                          | Qualitative Nominal   | Yes or no                                              |
| Time from intubation to start of therapy | Time from intubation to start of therapy                                                                                       | Discrete Quantitative | Days                                                   |

Association between early multimodal therapy and days of mechanical ventilation in the intensive care unit of the Fundación Santa Fe de Bogotá: A randomized controlled clinical trial.

Version 6.0

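### The three delirium-day secondary outcomes have no rule for death and no death-penalised companion outcome, so they tend to favour an arm with more early deaths

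*Protocol*

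**What the plan says.** Section 6.6 (Effectiveness) names eight secondary outcomes. Three count delirium: "Days of delirium until day 28", ICU time with delirium, and hospital days with delirium, all over the same 28-day window. The list also has a sedation count ("Days of sedation until day 28"), sedation-free days and ventilator-free days.

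The variable table in Section 6.11 treats these differently:

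- Delirium days: "Days with the presence of delirium", unit days, nothing about death. ICU time and hospital days with delirium have no row of their own.
- Sedation days: "Days with sedation", unit days, nothing about death.
- Sedation-free days: "28 days fewer days of sedation", with "It will be defined as 0 if the patient dies".
- Ventilator-free days: "It will be defined as 0 if the patient dies or has been ventilated for more than 28 days".
- The Barthel index, the mobility scale and grip strength are also 0 at death.

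Section 6.13 compares continuous variables between arms by t-test or Mann-Whitney, with no exception for these counts. Section 6.8 discusses lost participants and possible imputation but does not mention death. Annex 5 collects start and end dates for delirium and sedation and adds no rule.

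**The concern.** Fewer delirium days is the better result, and a patient can accrue delirium days only while alive. Someone who dies on day 2 without waking scores 0, the best possible value, while a survivor with a few days of delirium scores worse. If one arm has more early deaths, its average count is pulled down for a reason unrelated to less delirium.

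Three of the eight secondary outcomes are affected, and they are overlapping versions of one construct. A reader could not turn to a better-behaved delirium outcome in the same list, because there is none. For ventilation and sedation there is one.

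**Working it through.** The plan gives no figure of its own to reproduce. The check has three parts.

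**1. Is a death rule supplied anywhere?** The outcome list, variable table, missing-data section, analysis section and data-collection form were read together.

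| Outcome (secondary, to day 28) | Value at death | Companion outcome scored 0 at death |
|---|---|---|
| Delirium days | none | none |
| ICU time with delirium | none | none |
| Hospital days with delirium | none | none |
| Sedation days | none | sedation-free days |
| Ventilator-free days | 0 | not needed |

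**2. Direction, by hand.** Assumptions not in the documents: mean 5 delirium days in survivors and 0.5 in patients who die early, the same in both arms; mortality 33% in arm A and 23% in arm B.

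Mean count = (1 − mortality) × 5 + mortality × 0.5

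- Arm A: 0.67 × 5 + 0.33 × 0.5 = 3.350 + 0.165 = 3.515
- Arm B: 0.77 × 5 + 0.23 × 0.5 = 3.850 + 0.115 = 3.965
- Difference: 3.515 − 3.965 = −0.45 day, favouring the arm with more deaths

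With delirium-free days and death scored 0, the mean is (1 − mortality) × (28 − 5):

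- Arm A: 0.67 × 23 = 15.41
- Arm B: 0.77 × 23 = 17.71
- Difference: −2.30 days, against the arm with more deaths

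Simulating this scenario with 37 per arm and overdispersed survivor counts (gamma-Poisson, shape 1 to 5, an assumption) gives a standard error of the difference of about 0.8 to 1.2 days. A shift of 0.45 is therefore about half a standard error. Mann-Whitney falsely favours the arm with more deaths at p<0.05 in about 7% to 10% of runs, against about 2.5% by chance.

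**3. Sensitivity to other assumptions.** A second simulation used 37 per arm and 1,500 runs per setting, with the same underlying duration in both arms (no true effect). Durations were geometric with mean 4, 6 or 8 days, capped at 28. Deaths were spread evenly over the first 3 or the first 7 days. Days were counted only until death, and the test was Mann-Whitney.

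| Mortality, A vs B | Raw count, A minus B (days) | A falsely favoured, raw count | Free days with death = 0, A minus B | A falsely favoured, free days |
|---|---|---|---|---|
| 23% vs 23% | 0.00 to 0.04 | 2.2% to 3.2% | −0.04 to 0.04 | 2.2% to 3.3% |
| 33% vs 23% | −0.12 to −0.56 | 3.1% to 6.9% | −1.90 to −2.49 | 0.2% to 0.7% |
| 51% vs 23% | −0.40 to −1.65 | 7.1% to 31.5% | −5.57 to −6.67 | 0.0% |

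With equal mortality, two-sided rejection on the raw count was 4.4% to 5.9%, so there is no bias. With unequal mortality the raw count favoured the arm with more deaths in every setting. The last row puts the two ends of the protocol's background mortality range in opposite arms. It is an extreme, not a forecast.

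**The case against.** **The problem needs unequal mortality, and the protocol gives no reason to expect it.** This stands as a limit. Section 4 cites a 750-patient trial with no difference in 180-day mortality and a meta-analysis with no significant 28-day difference. Even so, unequal deaths can arise by chance in a trial this small. At a true 23% in both arms of 37, a gap of four or more deaths occurs in about a third of trials. That does not inflate the type I error, but it can make a single trial's delirium result misleading.

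**Only early deaths lower the count.** This also stands. A patient who dies late after prolonged delirium can add many days.

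**A reader might infer that the protocol expects 23% to 51% mortality, so that 9 to 19 of 37 patients per arm are affected.** The documents do not support that. Section 2 reports "high hospital mortality rates, ranging from 23% to 51" per cent as background on ventilated ICU patients in general. Section 6.2 selects a different population: it requires a Barthel index of at least 70 and excludes, among others, cardiac arrest and life expectancy under 180 days. Hospital mortality is not 28-day mortality, and multiplying the range by 37 counts every death rather than the early ones.

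**A reader might also count sedation days as a fourth unprotected outcome.** Sedation-free days, scored 0 at death, is already secondary and largely covers it. The day-2 example does not carry over either, because a sedated patient accrues sedation days until death. What remains is that the two sedation outcomes could disagree.

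**Handling of death is often left to a statistical analysis plan, and mortality is reported anyway.** Raw days while alive is a legitimate descriptive quantity, and all-cause mortality to day 90 is listed. But the protocol itself fixes death values for neighbouring variables in the same table and leaves delirium with none. Reporting mortality separately helps a careful reader but does not correct the delirium test.

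**Conclusion.** The point holds for the three delirium-day outcomes. As defined, they tend to favour an arm with more early deaths, and unlike ventilation and sedation, delirium has no outcome that counts death against an arm. The direction follows from the definition. The size does not: it is zero when mortality is equal, about 0.45 day under the illustrative assumptions (33% versus 23% mortality, 5 days in survivors, 0.5 in early decedents), and 0.12 to 0.56 day at the same mortality under the other durations and death times tried.

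The 2.3-day difference in free days should not be read as a corrected delirium effect. It measures a different quantity and arises because death is scored 0. It shows only that the direction no longer rewards death.

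The primary outcome and the sample size are untouched. This is worth correcting but does not threaten the trial.

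**What to change.** 1. Add one secondary outcome: days alive and free of delirium to day 28, set to 0 if the patient dies by day 28. This mirrors the existing rule for ventilator-free and sedation-free days. State the day explicitly, because those rules do not, and mortality is followed to day 90.
2. Make it the delirium outcome that is tested between arms.
3. State that days on which delirium cannot be assessed because of deep sedation or coma do not count as delirium-free. Otherwise a more deeply sedated arm would score better.
4. Keep the three delirium counts and sedation days, but report them descriptively, by survival status and next to mortality. They need not be deleted.

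Cost: delirium dates, sedation dates and mortality are already collected. The listed secondary outcomes need a small amendment, and any registration entry should match; both should be done before outcome data are seen. The downside is that the new outcome is a composite with death, so a difference may reflect mortality rather than delirium. The descriptive counts in step 4 let a reader tell the two apart.

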1. Oxygenation (O): The PaO2/FiO2 ratio > 150, arterial oxygen saturation > 90% with FIO2 0.4, PEEP ≤ 8 cm H2O and Tobin's index (fr/Vt) < 105. Each variable will be marked as yes or no.
2. Respiratory Mechanics (M): exhaled tidal volume greater than 5 ml/kg vital capacity > 10 ml/kg, maximum inspiratory pressure (MIP) ≤ -20 to 25 cmH2O, respiratory rate < 35 per minute, and values of PIM and PEM.
3. Acid-Base (A): paCO2 < 50 mmHg, pH > 7.32, lactic acid > 2, and venous saturation > 75%.
4. Hemodynamic (H): Systolic pressure > 90 or < 160, heart rate ≤ 140 per minute, the presence of arrhythmias and doses of vasopressors (high > 0.2 mcg (kg/min)
5. Airway (A): history of difficult airway and leak test results > 40%.
6. Clinical Component (+): Additional clinical factors, such as the presence of effective cough, management of secretions, the patient's neurological status, resolution of the underlying cause of intubation, and the manifestation of clinical signs of respiratory distress, as well were considered.

After extubation, several indicators will be carefully monitored to assess the patient's recovery and stability. The presence of dysphonia at 72 hours, maximum mobility measured by JH-HLM at 24 hours, and grip strength within the same period will be recorded. Additionally, the need for non-invasive mechanical ventilation at 48 hours will be evaluated, indicating whether it is required or not. The possible presence of dysphagia at 72 hours will also be documented, along with the timing of oral intake initiation, classified into two options: 1) between 12 and 24 hours, and 2) after 24 hours. The occurrence of extubation failure at 48 hours will be recorded, indicating whether

it occurred or not, and muscle strength will be measured using the MRC Scale at 24 hours to assess the patient's functional capacity after the extubation procedure.

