Fundación Santa Fe de Bogotá

April 8, 2024

|                                                         |                                                                                   |                     |                                                                                                                                                                                                                                                                                                                                                                                                                                                                                 |
|---------------------------------------------------------|-----------------------------------------------------------------------------------|---------------------|---------------------------------------------------------------------------------------------------------------------------------------------------------------------------------------------------------------------------------------------------------------------------------------------------------------------------------------------------------------------------------------------------------------------------------------------------------------------------------|
| Muscle strength with the medical research scale council | Evaluation of muscle strength in critically ill patients                          | Qualitative Ordinal | 
5, normal: full movement against full resistance
 
4+, good (+): full movement against gravity and strong resistance
 
4, good (-): full movement against gravity and minimal resistance
 
3+, regular (+): full movement against gravity only
 
3, regular (-): partial movement only against gravity
 
2, sparse: movement eliminated gravity
 
1 minimal: visible muscle contraction without movement
 
0 absent: total paralysis.
 |

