| Quantitative assessment of cognitive processing | 
Through standardized evaluation, in a directed activity that evaluates domains of isospacial/executive vision, naming, attention, language, memory, abstraction, and orientation.
 
The version that corresponds to the patient will be used like this:
 
Standard: for people with high school education levels and above.
 
 
• Basic: for people with illiteracy or low education
 
 
Blind: for people with significant impairment of visual function
 
Cognitive Processing Assessment (Montreal Cognitive Assessment)
 | Discrete Quantitative | Numeric                                                                                                                                                                      |
| Evaluation of functionality in daily activities | The patient's level of autonomy and independence will be assessed in basic daily activities of daily living, determining the level of functionality in these, supported by direct observation, clinical                                                                                                                                                                                                                                                                                                                                                                                            | Qualitative Ordinal   | 
7: Complete independence
 
6: Modified Independence
 
5: Supervised
 
4: Minimum attendance
 
3: Moderate assistance
 
2: Maximum assistance
 |

|                                         |                                                                                                                                                       |                         |                                                    |
|-----------------------------------------|-------------------------------------------------------------------------------------------------------------------------------------------------------|-------------------------|----------------------------------------------------|
|                                         | history, and reference from nursing staff and family/caregiver.

Functional Independence Measure (FIM).                                         |                         | 1: Full attendance                                 |

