## **Intervention**

### **Passive/Assisted Speech Therapy (Proprioceptive):**

Active/Assisted Speech Therapy (Neuromuscular Praxis)

The modified Medical Research Council (MRC) muscle strength scale will be implemented. The assessment of orofacial muscle qualities will begin. Buccinator, masseter, labial, and lingual muscle chains will be evaluated:

1. Cervical strength and mobility assessment.
2. Assessment of lower jaw positioning to verify closing strength and/or oral opening maintenance at rest.
3. Superficial facial sensitivity assessment in the middle, upper, and lower thirds bilaterally.
4. Palpation of orofacial muscle groups to verify muscle tone qualities.
5. Simple praxis movements will be requested from the patient to assess mobility ranges, reach, and strength.
6. Movements will be evaluated against gravity, then with resistance, and finally against resistance.
7. Based on the results, classification within the modified Medical Research Council muscle strength scale will be performed.

Fatigability tendency with repetition will also be considered.

Neck Flexion, Lateral Inclination, and Rotation:

- Superior Cervical Flexion: Works on the longus capitis, rectus capitis anterior, suprahyoid muscles (flexion of the upper cervical spine), and infrahyoid muscles (stabilizes the hyoid).

- Inferior Cervical Flexion: Works on the longus colli, platysma, anterior scalene, sternocleidomastoid.
- Rotation: Contralateral (all scalenes), sternocleidomastoid, Homolateral: longus capitis and colli, rectus capitis anterior.
- Lateral Inclination: Longus colli, all scalenes, and sternocleidomastoid.

Neck Extension, Lateral Inclination, and Rotation:

- Superior Cervical Extension: Iliocostalis and longissimus capitis, obliquus capitis (superior and inferior), rectus capitis posterior (major and minor), semispinalis and spinalis capitis, trapezius.
- Inferior Cervical Extension: Iliocostalis cervicis, longissimus and splenius cervicis, multifidus and rotatores, semispinalis and splenius cervicis, trapezius.
- Rotation: Contralateral: multifidus and rotatores, semispinalis capitis, upper trapezius, Homolateral: inferior obliquus capitis, splenius cervicis and capitis.
- Lateral Inclination: Iliocostalis cervicis, intertransversarii (cervical), longissimus capitis, superior obliquus capitis, splenius cervicis and capitis, trapezius.

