### Later to extubation:

- Dysphonia at 72 Hours: \_\_\_\_\_ (Yes/No)
- Maximum Mobility Extent by JH-HLM at 24 hours: \_\_\_\_\_
- Force Prehensile at 24 hours: \_\_\_\_\_
- Need of Ventilation Mechanics No Invasive to the 48 hours: \_\_\_\_\_ (Yes/No)
- Dysphagia to the 72 Hours: \_\_\_\_\_ (Yes/No)
- Start of Track Oral: \_\_\_\_\_ (1: 12-24 hours, 2> 24 hours).
- Failure Extubation at 48 hours: \_\_\_\_\_ (Yes/No)
- Force Muscular Measured with the scale MRC to the 24 hours: \_\_\_\_\_

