### Final observational:

#### Functionality and Stay:

- Index by Barthel to the Egress hospitable: \_\_\_\_\_
- Function cognitive measured by MOCHA: \_\_\_\_\_
- Test fast of sensitivity and skill: \_\_\_\_\_
- Days of Hospital Stay: \_\_\_\_\_ (the day when the intensivist informs transfer to the floor).
- Time of Stay in ICU: \_\_\_\_\_ (days).
- Mortality: \_\_\_\_\_ (yes/no)
- State of Independence Functional Measured by ADLs to the Egress Hospitable: \_\_\_\_\_
- State of Independence Functional Measured by ADLs to the Egress of the ICU: \_\_\_\_\_

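### The MRC muscle-strength outcome is one ordinal grade per patient with no muscle group, side, rater or summary rule, so grades are not comparable between patients and cannot be summed later.

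*Protocol*

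**What the plan says.** - **Role.** The PICOT table (section 3) lists MRC muscle strength among the secondary outcomes. Section 6.6 lists it as exploratory.
- **Definition (section 6.11).** The definition is "Evaluation of muscle strength in critically ill patients". The type is qualitative ordinal, with eight levels (0, 1, 2, 3, 3+, 4, 4+, 5) headed by "5, normal: full movement against full resistance".
- **Timing (section 6.7).** "muscle strength will be measured using the MRC Scale at 24 hours to assess the patient's functional capacity after the extubation procedure". No muscle is named.
- **Form (Annex 5, post-extubation block).** There is one blank, "Force Muscular Measured with the scale MRC to the 24 hours".
- **Procedure (Annex 1, speech therapy).** "The modified Medical Research Council (MRC) muscle strength scale will be implemented", and then "The assessment of orofacial muscle qualities will begin". The muscles are those of the cheeks, jaw, lips and tongue, with the neck. The physiotherapy part of Annex 1 describes no MRC test; it refers to an institutional protocol (AMB-REHF-PT-020) that is not included.
- **Blinding (section 6.1).** Only the day-90 evaluators and the data analysts are kept unaware of the arm.

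**The concern.** Each level of the MRC scale describes how one movement performs: against resistance, against gravity, or a visible contraction only. It grades a muscle, not a patient. A patient graded 4 in the arms and 2 in the legs has no defined code in this plan. Two patients with the same code can differ widely, and two raters can give the same patient different codes without either being wrong.

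The assessment is made 24 hours after extubation by staff who are not blinded, so the choice of muscle is open to influence from knowledge of the arm. At best this adds noise and hides a real strength effect. At worst it lets a difference between arms reflect which muscle was graded.

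This is a fault of data capture. A statistical analysis plan can choose how to combine item grades, but only if they were recorded.

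**Working it through.** **Text check.** The elements needed to reproduce an MRC outcome, set against the visible text:

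| Element | Where it would stand | What is there |
|---|---|---|
| Muscle groups | 6.7, 6.11, Annex 5 | none named |
| Side | same | none named |
| Assessing discipline | same | none named |
| Rule to combine grades | 6.11 | none; one ordinal grade |
| Time | 6.7, Annex 5 | 24 h after extubation |
| Test procedure | Annex 1 | speech therapy only (face and neck), not linked to the outcome |

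The same variable table is specific elsewhere. Grip strength names the dominant hand and a 24-hour window. NIF has separate rows for respiratory therapy and physiotherapy. The coin test gives a threshold for each hand. The Barthel index, also a score, is typed as discrete quantitative, whereas MRC is typed as ordinal; that supports reading the MRC entry as one grade rather than a sum.

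**Size of the precision loss.** The protocol states no power, standard deviation or effect for MRC, so there is no figure to reproduce. What follows is an illustration. Assumed, not in the documents: 6 or 12 muscle sites, equal correlation r between sites, and an effect acting on the strength shared by all sites. From the documents: 37 patients per arm and the eight levels.

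*Sample-size factor.* With unit variance per site, the mean of k sites has variance [1 + (k − 1)r]/k. Grading one site therefore needs k/[1 + (k − 1)r] times as many patients as using the mean. For k = 12:

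- r = 0.5: 12/6.5 = 1.85
- r = 0.7: 12/8.7 = 1.38
- r = 0.9: 12/10.9 = 1.10

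For k = 6: 6/3.5 = 1.71, 6/4.5 = 1.33 and 6/5.5 = 1.09.

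*Power.* Simulation with 12 sites, 37 per arm, two-sided Mann-Whitney test at 0.05, a difference of 0.6 SD in shared strength and 2,000 trials per row. Site strength was normal (mean 3.6, SD 0.9) and cut into the eight levels at 0.5, 1.5, 2.5, 3.25, 3.75, 4.25 and 4.75.

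| r | Sum of 12 sites | One site | Median grade over all sites |
|---|---|---|---|
| 0.5 | 65.3% | 39.4% | 60.8% |
| 0.7 | 67.6% | 52.4% | 66.0% |
| 0.9 | 70.4% | 64.4% | 68.6% |

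Loss against the sum if one site is graded: 25.9, 15.2 and 6.0 points. Loss if the rater gives a median over all sites: 4.5, 1.6 and 1.8 points. Simulation error is about one point (√(0.65 × 0.35/2000) = 0.011).

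**The case against.** The best case for the plan has four parts.

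1. **The table lists response levels and does not say that only one is stored.** The Annex 5 blank carries no coding, and the electronic form is not shown, so a sum could be entered. This is possible, but the ordinal type and the single blank point the other way, and nothing tells a rater to sum.
2. **Limb testing may be described in the institutional physiotherapy protocol.** It may. The protocol cites that document for delivering treatment and does not tie it to the MRC outcome.
3. **Item scoring often sits in a form manual or analysis plan.** That holds for how items are combined. It does not hold where the document itself fixes one ordinal grade and one blank.
4. **The stakes are low.** This stands. Section 6.6 makes the outcome exploratory, and grip strength, Barthel and JH-HLM cover neighbouring ground.

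Four stronger readings are tempting and are not supported.

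- **A reader might infer that face and tongue grades will be reported as general strength.** The speech-therapy text uses a modified scale, sits under intervention, and gives neither the 24-hour time nor a link to the outcome. Section 6.7 speaks of functional capacity. The gap permits such a mix-up; the document does not plan it.
- **A reader might infer that nearly half the information is lost** (74/1.85 = 40 effective patients). That holds only for one graded site at r = 0.5 with 12 sites.
- **A reader might take the mention of MRC beside ICU-acquired weakness in the respiratory-therapy annex as this trial's rationale for the scale.** It describes a cited study.
- **A reader might charge the FIM variable with the same fault.** Its row speaks of "determining the level of functionality in these", meaning several daily activities, and lists levels 1 to 7. However, section 6.7 refers to Annexes 3 and 4, Annex 3 is a figure not shown, and the form line reads "State of Independence Functional Measured by ADLs to the Egress Hospitable" without naming FIM. An item list may exist, so no error is established.

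**Conclusion.** The point holds for MRC. As written, the outcome is a single grade of an unspecified muscle, chosen by an unspecified and unblinded rater, and the item grades needed for a summary score would not exist at analysis. That rests on the text alone.

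The loss of precision is a consequence whose size the documents cannot settle. Under the assumptions shown it lies between about 2 and 26 power points. The lower end (about 2 to 5) applies if raters already give a grade typical of all sites, the upper end if one site is graded and r = 0.5. The lack of comparability is the firmer ground for change.

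The primary outcome, sample size and safety outcomes are not affected. The change is worth making because it is cheap and cannot be made after data collection.

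**What to change.** - In section 6.11, define the MRC outcome as the sum of grades over a fixed, named list of limb muscle groups tested on both sides, state the numeric value of 3+ and 4+ in that sum, and name the discipline that assesses it.
- In Annex 5, replace the single blank with one field per muscle group and side.
- Store the speech-therapy face and neck grade as a separate variable with its own name.
- For FIM, check whether Annex 3 and the electronic form record a level per activity. If they do, let the 6.11 row store the total.

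Cost: a few more form fields and some minutes per assessment, by therapists who are already on the unit and already assess these patients. No extra staff or visits.
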